# Cryoneurolysis’ outcome on pain experience (COPE) in patients with low-back pain: study protocol for a single-blinded randomized controlled trial

**DOI:** 10.1186/s12891-021-04320-7

**Published:** 2021-05-19

**Keywords:** Low-back pain, Cryoneurolysis on lower-back pain, Cryoanalgesia, Cryoneurolysis, Cryoneuroablation, Radiofrequency ablation

## Abstract

**Background:**

Low-back pain, including facet joint pain, accounts for up to 20 % of all sick leaves in DenmarkA proposed treatment option is cryoneurolysis. This study aims to investigate the effect of cryoneurolysis in lumbar facet joint pain syndrome.

**Methods:**

A single-center randomized controlled trial (RCT) is performed including 120 participants with chronic facet joint pain syndrome, referred to the Department of Neurosurgery, Aarhus University Hospital. Eligible patients receive a diagnostic anesthetic block, where a reduction of pain intensity ≥ 50 % on a numerical rating scale (NRS) is required to be enrolled. Participants are randomized into three groups to undergo either one treatment of cryoneurolysis, radiofrequency ablation or placebo. Fluoroscopy and sensory stimulation is used to identify the intended target nerve prior to administrating the above-mentioned treatments. All groups receive physiotherapy for 6 weeks, starting 4 weeks after treatment. The primary outcome is the patients’ impression of change in pain after intervention (Patient Global Impression of Change (PGIC)) at 4 weeks follow-up, prior to physiotherapy. Secondary outcomes are a reduction in low-back pain intensity (numeric rating scale) and quality of life (EQ-5D, SF-36) and level of function (Oswestry Disability Index), psychological perception of pain (Pain Catastrophizing Scale) and depression status (Major Depression Inventory).

Data will be assessed at baseline (T0), randomization (T1), day one (T2), 4 weeks (T3), 3 (T4), 6 (T5) and 12 months (T6).

**Discussion:**

This study will provide information on the effectiveness of cryoneurolysis vs. the effectiveness of radiofrequency ablation or placebo for patients with facet joint pain, and help to establish whether cryoneurolysis should be implemented in clinical practice for this patient population.

**Trial registration:**

The trial is approved by the ethical committee of Central Jutland Denmark with registration number 1-10-72-27-19 and the Danish Data Protection Agency with registration number 666,852. The study is registered at Clinicaltrial.gov with the ID number NCT04786145.

## Background

Low-back pain affects 1 out of 7 individuals in Denmark, and accounts for up to 20 % of total sick leave causes [1]. Approximately 10 % will develop chronic and disabling low-back pain [1].

In 15–52 % of patients with chronic low-back pain, the reported cause is facet joint syndrome [2]. Facet joint syndrome can cause localized low-back pain and referred pain to adjacent structures in a pseudo-radicular pattern, making the underlying diagnosis difficult to confirm without the use of diagnostic blocks [2]. Neurologic symptoms, such as paresis, are usually absent despite 37 % of patients having a neuropathic pain component [3, 4], mainly presenting as radicular-like leg pain [5].

Current treatment options for low-back pain from facet joint syndrome include conservative therapy, medical management, procedural interventions (e.g. neurotomy, facet joint injection, spinal fusion surgery) [6]. Additionally, tailored exercise programs have been shown to reduce pain [6]. However, patients will sometimes fail an exercise program due to pain aggravation; a possible reason is that facet joint syndrome may be considered a “biomechanical” pain, typically made worse on movement [3]. Furthermore, significant myofascial spasms in the paravertebral region may be present [3]. Known predictors for chronification of low-back pain from facet joint syndrome are high pain intensity, high level of generalized pain, low socio-economic status, weak social network, sick leave, co-morbidity, fear of movement and inadequate coping strategies, which underline the complexity of the condition [1].

### Cryoneurolysis

Cryoneurolysis is a medical procedure that temporarily destroys nerve conduction along peripheral nerve pathways. The procedure, during which a small probe is inserted in order to freeze the target nerve, can facilitate complete regeneration of the structure and function of the affected nerve [4]. It has been proposed as a procedural intervention option for facet joint syndrome and has been claimed to be superior to other peripheral nerve ablation methods [7–9]. In two studies, cryoneurolysis proved superior in providing pain relief by freezing the medial branch nerve (at minus 80 degrees Celsius) compared to intraarticular injections or pericapsular block [8, 10].

### Radiofrequency ablation

Another method is radiofrequency ablation (RFA). This is a procedure, during which a thin insulated needle with an active RF conducting tip is inserted, to destroy the targeted nerve tissue using radiofrequency generated heat energy [11–14]. It is shown to be effective in pain relief (at 80 degrees Celsius). A review from 2007 found the level of evidence for the efficacy of radiofrequency or cryoneurolysis to be moderate for short and long-term pain relief [3]. One prospective trial found a significant reduction in pain intensity and improvement in daily activities at all follow-up times up to one year [10].

Current literature investigating the effect of cryoneurolysis on facet joint pain syndrome is still sparse. Therefore, the need for a randomized controlled trial to evaluate the effect of cryoneurolysis on low-back pain due to facet joint syndrome is urgent.

## Methods: participants, interventions, and outcomes

### Primary and secondary objectives

The primary aim is to compare the effect of cryoneurolysis to placebo for facet joint pain syndrome. Secondary aims are to compare the effect of cryoneurolysis to RFA in facet joint pain syndrome and to investigate whether pre-defined parameters are independent predictors of outcome in cryoneurolysis in lumbar facet joint pain syndrome.

### Study design

The study is a single-center, blinded randomized controlled trial with two intervention arms and one placebo arm with allocation ratio of 1:1:1. One group receives one treatment of cryoneurolysis, the second group receives one treatment of RFA and the third group receives placebo (control group).

### Study setting

The study is performed at Aarhus University Hospital, Denmark.

### Eligibility criteria

All patients above the age of 18 years, with low-back pain from facet joint syndrome of more than three months’ duration, with or without neuropathic pain component and with moderate pain intensity defined by numeric rating scale (NRS-11) ≥ 4 are eligible for the study. Eligible patients receive a diagnostic anesthetic block, where a reduction of pain intensity ≥ 50 % on a numerical rating scale (NRS-11) after 60 min is required to be enrolled. NRS-11 is a widely used and validated 11-point scale for patient self-reporting of pain [15, 16]; each patient is asked to assess their pain on a scale from 0 to 10, where 0 is no pain and 10 is the worst imaginable pain.

#### Exclusion criteria

Presence of nerve root or spinal canal compression; signs of inflammatory or erosive processes in the spine verified on magnetic resonance imaging (MRI).Neurological deficits i.e. symptoms of nerve root compression; tingling, numbness, weakness/ paresis, and reflex loss in the lower extremities.Major co-morbidity.Anti-thrombotic or anti-platelet treatment which cannot be paused for a week.Active malignancies.Chronic inflammatory disease.Known severe psychiatric disease. Patients with mild and well-treated depression and anxiety are not excluded.

### Sample Size

Based on our pilot study (not published), we postulate that 50 % of the participants who receive an active treatment (cryoneurolysis or radiofrequency ablation) and 5 % of the placebo group will report a significant improvement of change in pain after intervention, equivalent to Patient Global Impression of Change (PGIC) ≤ 2, at 4 weeks’ follow-up. Sample size is calculated by Fisher’s Exact test based on the above-mentioned and with 80 % power (two-tailed) and α = 0.025, 120 participants (40 per group) are needed in the study, which also includes a 25 % margin for loss to follow-up. The power of the study is the probability that there is a significant difference between each of the two intervention groups, where in each of the two tests a significant level of 2.5 % is used, so that the overall significance level becomes 5 %.

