### Study intervention methods

The interventions are performed under local anesthetic with lidocaine 1 % cum adrenaline and if needed additional intravenous analgesics are given during the procedure. The Universal Protocol for surgery [17] and aseptic technique is performed. In prone position and after surgical marking guided by fluoroscopy based on the same vertebral levels as concluded from the anesthetic block, 20–30 milliliters of lidocaine 1 % cum adrenaline is administered in the skin. Fluoroscopy and sensory stimulation are used to find the intended target nerve (medial branch nerve) of the facet joint pain generator at three levels bilaterally. For every facet joint two introducer needles are inserted according to the anatomic course of the medial branch nerve; (1) into the angle between the superior articular and the transverse process and (2) onto the inferior border of the transverse process at the level of the inferior articular process (3) (see Fig. 1). For cryoneurolysis and placebo, generic branded 14G introducer needles are used, while for RFA, 22G radiopaque RFA cannula needles (105/PMF22-100-5) are used. To ensure proper placement of the probe close to the medial branch nerve, the cut-off threshold for the sensory stimulation test is 0.5 volts for cryoneurolysis and RFA with pulse time of 1 milliseconds and frequency of 50 Hz [3, 14, 18]. When proper probe placement is achieved, 1 ml of lidocaine 1 % cum adrenaline is administrated per location through each introducer needle before the selected treatment is given.

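### The stated sample-size inputs give 27 per arm (31 if both comparisons must succeed), not 40, so 80 % power and 120 participants do not belong together

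*Protocol article*

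**What the plan says.** All inputs stand in the Sample Size section of the protocol article.

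- **Response rate, active arms (PGIC of 2 or lower at 4 weeks):** "50 % of the participants who receive an active treatment (cryoneurolysis or radiofrequency ablation".
- **Response rate, placebo arm (same definition):** "5 % of the placebo group will report a significant improvement of change in pain after intervention". Both rates are attributed to an unpublished pilot.
- **Test:** "Sample size is calculated by Fisher’s Exact test".
- **Error rates:** "80 % power (two-tailed) and α = 0.025".
- **Multiplicity (figures in per cent):** "in each of the two tests a significant level of 2.5 % is used, so that the overall significance level becomes 5".
- **Meaning of power:** "The power of the study is the probability that there is a significant difference between each of the two intervention groups". The comparator is not named.
- **Result:** "120 participants (40 per group) are needed in the study", with a 25 % allowance for loss to follow-up already counted in that number.

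The Study design section gives 1:1:1 allocation. The section names no other margin, no higher target power and no other analysis as a reason for 40 per group.

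**The concern.** The section sets out a complete calculation: rates, test, sidedness, alpha, power and loss. A reader should be able to put these in and obtain 40 per group, and cannot. The rates of 50 % and 5 % are far apart, and at that distance about 20 evaluable patients per arm are enough even for an exact test at 0.025.

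What is at stake is the reliability of the planning statement. It is the stated justification for the number randomised, including those given a placebo procedure, and readers will cite it when they interpret the primary result. As printed, either the 80 % is not the power of a 120-patient trial at these rates, or one of the printed rates, the power or the loss figure is not the one that was used.

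**Working it through.** **Inputs (Sample Size section).** Active response 0.50; placebo response 0.05; two-sided Fisher test, significant if p ≤ 0.025; target power 0.80; loss 0.25; equal arms.

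**Formulas.** With n evaluable per arm, X ~ Bin(n, 0.50) and Y ~ Bin(n, 0.05):

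- Per comparison: power = Σ over x, y of P(X = x)·P(Y = y)·1[p(x, y) ≤ 0.025].
- Both comparisons, sharing one placebo arm: power = Σ over y of P(Y = y)·{Σ over x of P(X = x)·1[p(x, y) ≤ 0.025]}².
- Randomised per arm = n / (1 − 0.25), rounded up.

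All 2×2 tables were enumerated, so there is no simulation error.

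**Step 1: try to reproduce 40 per group at 80 % power.**

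| Reading | Evaluable per arm | Exact power | Randomised per arm | Total |
|---|---|---|---|---|
| Per comparison | 19 | 78.4 % (too few) | – | – |
| Per comparison | 20 | 81.8 % | 20/0.75 = 26.7, so 27 | 81 |
| Both comparisons | 22 | 78.3 % (too few) | – | – |
| Both comparisons | 23 | 81.7 % | 23/0.75 = 30.7, so 31 | 93 |
| Both, alpha halved again to 0.0125 | 26 | 80.0 % | 26/0.75 = 34.7, so 35 | 105 |

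The last row is the strictest 80 % variant tried. It is not what the section says, and it still falls short of 40.

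**Step 2: check whether an approximate formula explains the gap.** With mean rate 0.275, z = 2.2414 for alpha 0.025 two-sided and z = 0.8416 for 80 % power:

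n = [2.2414·√(2·0.275·0.725) + 0.8416·√(0.50·0.50 + 0.05·0.95)]² / 0.45² = [1.4154 + 0.4591]² / 0.2025 = 17.35, so 18 per arm.

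The continuity correction raises this to 21.6, so 22 per arm, and 22/0.75 = 29.3, so 30 randomised. The choice of formula or software does not close the gap.

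**Step 3: check whether cryoneurolysis versus radiofrequency ablation explains it.** Both are assigned 50 %, so there is no planned difference from which to derive a sample size.

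**Step 4: work back from 40 per arm.** 40 × 0.75 = 30 evaluable.

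| Evaluable per arm | Per comparison | Both comparisons |
|---|---|---|
| 30 (40 less 25 %) | 96.4 % | 93.3 % |
| 32 (40/1.25) | 97.6 % | 95.5 % |
| 40 (no loss) | 99.4 % | 98.9 % |

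None of these is near 80 %.

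**Step 5: see what other inputs could lie behind 40 (illustration only; these inputs are assumed).** With 30 evaluable per arm, power per comparison is 82.7 % for 40 % versus 5 %, and 84.8 % for 50 % versus 10 %. A 95 % target for both comparisons needs 32 evaluable, and 32 × 1.25 = 40. The article supports none of these over another. They show only that a reader cannot tell which calculation was done.

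**The case against.** The strongest reply is that the error does no harm. At the stated rates, 120 participants exceed 80 % power on every reading tried, even after the full 25 % loss. No patient number, test, alpha level or analysis has to change. All of that stands, and it limits the point to a correction of reporting. Deliberate rounding up is also possible, but the section says that 120 are needed and names one margin, already included. The gap of 39 participants (120 − 81), or 27 on the joint reading (120 − 93), is large for unstated rounding.

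A reader might go further and infer three things that the article does not support.

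- **That the trial is underpowered.** At 50 % versus 5 % the opposite is true.
- **That a null result could not be read against the stated 80 %.** If the postulated rates hold, 80 % is a valid lower bound and a null result is more informative than claimed. If they do not hold, the same is true of any power statement, and the mismatch adds nothing.
- **That 5 % placebo response is too low and power therefore collapses.** Lidocaine "is administrated per location through each introducer needle before the selected treatment is given", so all three arms receive it, along with needle placement. Pre-inclusion screening puts the duration of the diagnostic block at two to three hours, while the endpoint is at 4 weeks. Nothing in the article contradicts the 5 %. A steep loss of power appears only if placebo response rises while active response stays at 50 %: 66.7 % per comparison at 15 % placebo response, with 30 evaluable. If both rise together, power per comparison stays at about 92 % (55 % versus 10 %) or 89 % (60 % versus 15 %). All of these rates are assumptions.

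**Conclusion.** The point holds as an arithmetic inconsistency in the Sample Size section. The stated inputs require 81 participants per comparison-wise power, or 93 for joint power, against the 120 said to be needed. With 120 randomised and 25 % lost, power is about 96 % per comparison and 93 % for both, not 80 %. The direction is safe, so the adequacy of the trial at its stated rates is not in doubt.

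The conclusion rests on the printed rates, the exact two-sided Fisher test at 0.025, independent arms and loss handled as n/(1 − 0.25). It does not depend on which definition of power was meant, since neither gives 40. The article alone cannot show whether an input was misreported or a reason for the larger number was left out.

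**What to change.** Keep 120 participants. State whether power is per active-versus-placebo comparison or for both jointly, then do one of the following.

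1. **If the printed rates are the planning rates,** restate the result along these lines: *With 40 per arm (30 evaluable after 25 % loss), the two-sided Fisher's exact test at 0.025 has about 96 % power for each active-versus-placebo comparison and about 93 % power for both, assuming 50 % versus 5 % response.*
2. **If 120 came from other inputs,** correct the rates, target power or loss figure that was misreported, so that the calculation leads to 40 per arm.

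A sensitivity statement is optional. If one is added, mark it as an assumption and name the definition of power. With active response held at 50 % and 30 evaluable per arm, 80 % power holds up to about 11 % placebo response per comparison (81.6 % at 11 %), but only to just under 9 % for both comparisons (79.7 % at 9 %, 70.7 % at 11 %). Quoting the 11 % limit without saying that it is per comparison would mislead.

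The cost is a change of wording. No additional participants, data or analyses are needed.

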### Statistical analysis

Statistical analysis will be conducted by a researcher or statistician blinded for treatment allocation after follow-up is finished. No interim analysis will be performed.

Characteristics of the patients will be presented using descriptive statistics (mean (SD), median (range) or proportion) to assess if balanced groups were obtained after randomisation. The primary analysis will be conducted according to the intention-to-treat principle. In a secondary analysis, a per-protocol analysis shall be conducted.

For the primary outcome, PGIC at 4 weeks, Fisher’s exact test with α = 0.025 will be used on the group of units (cryoneurolysis, radiofrequency ablation or placebo) and tested twice (a “repeated measures” t-test) to investigate if there is a significant improvement of change in pain after intervention, equivalent to PGIC ≤ 2, at 4 weeks’ follow-up. If there are any clinically relevant disbalances in prognostic factors, such as age, gender, pain severity, the analysis will be adjusted for these potential confounders.

For the secondary outcomes, longitudinal analysis is used at multiple follow-up times as repeated measures data. However, if the data are not suitable for the longitudinal analysis model, another relevant statistical model is used. The repeated measurements provide reduced error, increased statistical power and, critically, a means to study the efficacy of cryoneurolysis and determinants of systematic changes secondary outcome over the follow-up time [21] Our data panels allow for measuring change in outcomes at the individual level. Outcomes will be analyzed with analysis of covariance (ANCOVA), including baseline values of the respective outcomes as covariates [22].

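### Both primary tests stay at 0.025 even after one has succeeded; Holm's step-down rule keeps the same 5 % overall level and never has less power

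*Protocol article*

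**What the plan says.** The Sample Size section plans Fisher's exact test "with 80 % power (two-tailed) and α = 0.025". It describes two tests, "where in each of the two tests a significant level of" 2.5 % applies, "so that the overall significance level becomes 5" %. The Statistical analysis section repeats the rule for the primary outcome: Fisher's exact test at α = 0.025 "will be used on the group of units (cryoneurolysis, radiofrequency ablation or placebo) and tested twice".

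Neither section lets the second test use a larger level once the first has succeeded. The decision rule is therefore a fixed Bonferroni split, stated in two places. The section on primary and secondary objectives names cryoneurolysis versus placebo as the only primary aim.

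**The concern.** Bonferroni guards against two possible false rejections by giving each half of the 5 %. After one hypothesis has been rejected, only one is left that could still be rejected falsely, so the full 5 % is available for it. The plan does not use this.

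The loss occurs in one situation: one test has p ≤ 0.025 and the other has p above 0.025 but no more than 0.05. The plan must then report the second comparison as not significant although its 5 % error budget would allow a positive conclusion. That second comparison can be cryoneurolysis versus placebo, the trial's main question, with radiofrequency ablation already shown to beat placebo.

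The point is about the decision rule. It does not depend on the conservatism of Fisher's test, and the error guarantee holds whichever two pairs are meant.

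**Working it through.** **Inputs from the protocol article**
- Level per test 0.025, overall level 0.05, two-sided, Fisher's exact test (Sample Size; Statistical analysis).
- Response rates: "50 % of the participants who receive an active treatment (cryoneurolysis or radiofrequency ablation") and "5 % of the placebo group will report a significant improvement" (Sample Size).
- 40 per arm, allocated 1:1:1, with a 25 % margin for loss: 40 × 0.75 = 30 evaluable per arm. On the other reading of the margin, 40 / 1.25 = 32.

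**Assumptions of mine.** The two tests are each active arm versus placebo; the text does not name the pairs clearly. Response rates other than 50 % and 5 % are not in the document.

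**The plan's own figures.** The alpha arithmetic reproduces: 0.025 + 0.025 = 0.05. The sample size does not. Fisher's test at 0.025 with 50 % versus 5 % reaches 80 % power at 20 evaluable per arm (81.8 %), which is 20 / 0.75 = 26.7, so 27 per arm or 81 in total, against the stated 120. That is a separate matter, but it explains why power at the stated rates is already high.

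**Holm's rule keeps 5 %.** Order the p values. Reject the first hypothesis if the smaller p ≤ 0.025; only then reject the second if the larger p ≤ 0.05.
- Both nulls true: any false rejection needs the smaller p ≤ 0.025, with probability at most 0.025 + 0.025 = 0.05.
- One null true: a false rejection needs that p ≤ 0.05, with probability at most 0.05.

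No independence is needed, so the shared placebo arm does no harm. Everything rejected at 0.025 is also rejected under Holm, so power cannot fall.

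**Power by exact enumeration.** For each placebo count z, let A(z) and B(z) be the probabilities that an active arm gives a Fisher p ≤ 0.025 and p ≤ 0.05. Subscripts C and R denote cryoneurolysis and radiofrequency ablation. Each quantity below is averaged over the binomial distribution of z.
- Both significant, plan: A_C · A_R
- Both significant, Holm: A_C · B_R + B_C · A_R − A_C · A_R
- Cryoneurolysis significant, plan: A_C
- Cryoneurolysis significant, Holm: A_C + (B_C − A_C) · A_R

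Results (plan → Holm):

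| Cryo / RFA / placebo | Evaluable per arm | Both significant | Cryo vs placebo |
|---|---|---|---|
| 50/50/5 % (protocol) | 30 | 93.4 → 96.5 % | 96.4 → 98.0 % |
| 50/50/5 % (protocol) | 32 | 95.5 → 97.8 % | 97.6 → 98.7 % |
| 50/50/5 % (protocol) | 40 | 98.9 → 99.6 % | 99.4 → 99.8 % |
| 50/50/10 % (assumed) | 30 | 75.3 → 84.2 % | 84.8 → 89.3 % |
| 50/50/10 % (assumed) | 40 | 91.4 → 95.4 % | 95.2 → 97.2 % |
| 50/50/15 % (assumed) | 30 | 51.5 → 63.9 % | 66.7 → 72.9 % |
| 50/50/15 % (assumed) | 40 | 73.5 → 82.1 % | 83.7 → 88.0 % |
| 35/50/5 % (assumed) | 30 | 68.1 → 77.8 % | 69.3 → 78.3 % |

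The chance of at least one success is the same under both rules (99.4 % at 50/50/5 % with 30 per arm).

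**Error rate by the same enumeration.** Over a grid of response rates, with both nulls true or only one, the largest familywise error under Holm was 2.6 % at 30 per arm and 3.4 % at 40, both below 5 %.

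**Worked example, 30 per arm.** Placebo 2/30, radiofrequency ablation 15/30: p = 0.0004. Cryoneurolysis 9/30: p = 0.042. Under the plan cryoneurolysis is negative. Under Holm 0.0004 ≤ 0.025, so the second test is made at 0.05, and 0.042 ≤ 0.05 is positive.

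**The case against.** **Bonferroni is valid.** It is prespecified and delivers the stated 5 %, so this is lost efficiency and not an error in type I control. That stands.

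**The gain is small at the plan's own inputs.** It is 1.6 points for cryoneurolysis versus placebo and about 3 points for both, with 30 per arm, and less with 40. Power already exceeds the 80 % target. The larger gains need rates that the document does not give, and they shrink if fewer patients are lost. All of this stands. Against it, the 5 % placebo rate rests on an unpublished pilot, the placebo is an invasive sham with local anaesthetic, and the outcome is self-reported. A higher placebo response is a realistic possibility, and that is where the rule could decide the result.

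**Power for both comparisons is not the primary aim.** With equal active rates, the gain for cryoneurolysis alone is half the gain for both. This is correct, and the table shows both columns.

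**Another repair may fit better.** Testing cryoneurolysis versus placebo first at 0.05 would match the stated primary aim and give that comparison more power (91.4 % against Holm's 89.3 % at 50/50/10 %, 30 per arm). This is a legitimate alternative, but it requires a decision on the ranking of the hypotheses. Holm needs none and already improves on the stated rule.

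**Holm is not wholly free.** Bonferroni has simple simultaneous 97.5 % confidence intervals that match its tests; Holm does not. The article plans no such intervals, so nothing planned is lost. Nor does a p value between 0.025 and 0.05 prove a real effect; it is only enough to reject within the 5 % budget.

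**A separate analysis plan might contain a step-down rule.** It is not at hand. The article, however, states 0.025 for both tests in two sections.

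**Conclusion.** The concern holds. The stated rule leaves alpha unused that could be spent at no cost to the 5 % overall level. The guarantee that Holm is at least as powerful rests on no assumption about rates or pairs.

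The size of the benefit does depend on assumptions. It is modest at the protocol's rates. With 30 evaluable per arm, it becomes about 9 to 12 points for showing both effects if placebo response is 10 to 15 %, and 9 points for cryoneurolysis versus placebo if its response is 35 % with radiofrequency ablation at 50 % and placebo at 5 %. These figures take the tests to be each active arm versus placebo. The change should be made because it is a uniform improvement; the present rule is not invalid.

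**What to change.** In Sample Size and in Statistical analysis, replace the fixed level of 0.025 in each test by Holm's procedure, for example: *The two primary comparisons are tested by Holm's procedure at an overall two-sided level of 5 %. The smaller p value is compared with 0.025; if it is significant, the larger is compared with 0.05; if it is not, neither comparison is significant.* Name the two comparisons in the same sentence.

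Keep the sample size. Planning at 0.025 per test remains a conservative basis for it.

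The cost is one sentence in a dated amendment before unblinding. The article plans no interim analysis and a blinded analysis after follow-up ends, so the change can still be prespecified if the data have not been unblinded. No patient procedure changes. If confidence intervals matched to the tests are wanted, their construction needs a further line.
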